### Safety

All adverse events, regardless of their possible association with the disease or study treatment, are recorded. Adverse events are considered to be serious if the investigator determines that they jeopardize the patient, are life-threatening, or could result in hospitalization, disability or death.

### Data and safety monitoring board

To promote consistent study execution at each participating center, independent monitoring visits are performed to supervise trial progress, ensuring that it is conducted, recorded and reported in accordance with the protocol, standard operating procedures, GCP and the applicable regulatory requirements.

The Data and Safety Monitoring Board consists of three independent hepatologists who are not members of the end-point committee and an independent statistician. The board protects the ethical interests and safety of the patients by reviewing interim analyses. The board is empowered to recommend termination of the study on the basis of safety concerns or as soon as sufficient evidence indicates that RGT plus ETV is statistically superior to ETV alone, or that RGT plus ETV does not provide a significant advantage over ETV alone.

### Ethics

The study protocol, written informed consent and posters were approved by the 302nd Military Hospital Ethics Review Committee (2013145D), and were accepted by the ethics committees at each of the institutions involved, and have been performed according to the Declaration of Helsinki.

The names of all ethical bodies in the various centers involved are the 302nd Military Hospital Ethics Review Committee, Fuyang No 2 People’s Hospital Ethics Review Committee, 88th Hospital of PLA Ethics Review Committee, First Affiliated Hospital of Zhengzhou University Ethics Review Committee, Fuzhou Infectious Diseases Hospital Ethics Review Committee, First Affiliated Hospital of Wenzhou Medical University Ethics Review Committee, First Affiliated Hospital of Third Military Medical University Ethics Review Committee, Guangzhou No 8 People’s Hospital Ethics Review Committee, Shanghai Public Health Clinical Center Ethics Review Committee, Affiliated Hospital of Chengdu University of Traditional Chinese Medicine Ethics Review Committee and Tianjin Second People’s Hospital Ethics Review Committee.

### Statistical methods

The randomized subjects who have taken at least one dose of study drug and are evaluated for at least once curative effect after taking medication, constitute the full analysis set and safety analysis set. Those who complete all the visits comprise the per-protocol set. The statistical analysis will be performed using SAS 9.1 software (SAS Institute, Cary, NC, USA). The overall loss rate due to adverse events of each group will be calculated. When subjects enter the trial, they are assessed for demographic data, baseline condition and other essential information and are compared between groups. Cumulative incidence of HCC and overall survival rate will be determined by Kaplan–Meier analysis, and the log-rank test will be used for treatment comparisons. Changes from baseline in liver histology (METAVIR score) as well as in liver and spleen imaging (type B ultrasound) between the two groups will be compared by the Cochran–Mantel–Haenszel test. Changes from baseline in serum markers for liver fibrosis and liver function, transient electrograph (FibroScan) and TCM syndrome between the two groups will be compared by a covariance or non-parametric test. The statistical significance is defined as a two-sided *P* <0.05.

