
**Figure 1 Fig1:**
[figure not shown]
**Flow chart of the current trial.** ETV, entecavir; HBV, hepatitis B virus; HBsAg, hepatitis B surface antigen; HCC, hepatocellular carcinoma; RGT, tablet of compound *biejia ruangan*; TCM, traditional Chinese medicine.

This study is being conducted in accordance with the ethical principles of the Declaration of Helsinki and is consistent with GCP guidelines and applicable local regulatory requirements. Written informed consent is obtained from all randomly assigned patients.

The primary end points in this study are the occurrence of HCC or liver-related mortality. HCC is diagnosed either histologically or clinically based on guidelines proposed by the Chinese Liver Cancer Study Group [19]. According to these criteria, patients are considered positive for HCC if they have one or more risk factors (hepatitis B or C virus infection, or cirrhosis) and one of the following: (1) serum α-fetoprotein (AFP) >400 ng/mL and a positive finding on at least one of three typical imaging studies [dynamic computed tomography (CT), dynamic magnetic resonance imaging (MRI) or hepatic angiography] or (2) serum AFP <400 ng/mL and positive findings on at least two of the three imaging studies. A positive finding for typical HCC on dynamic CT or MRI is defined as increased arterial enhancement followed by decreased enhancement compared with the liver (washout) in the portal or equilibrium phase. Liver-related mortality is defined as death caused by hepatic decompensation (regardless of etiology) or HCC.

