Secondary end points are disease progression and overall survival rate. Disease progression is defined as either histological progression reflected by an increase in METAVIR score of at least 1 point or clinical progression reflected by the occurrence of decompensated cirrhosis. Decompensated cirrhosis is defined by the development of complications of portal hypertension (ascites, variceal hemorrhage, hepatic encephalopathy or spontaneous bacterial peritonitis) and/or liver insufficiency (jaundice). Following previous studies [20, 21], liver biopsies are collected at three defined time points: before the start of randomization (unless a biopsy has been performed within 3 months of randomization), at week 72 of the double-blind treatment and at month 24 of the open-label treatment during follow-up. Every patient with liver biopsy of at least six portal tracts is included in the study. To ensure the quality of liver tissue specimens for pathological assessment, liver biopsies in all centers is performed using unified 16G liver biopsy needles and a modified Jamshidi Menghini needle (Allegiance Corporation, McGaw Park, IL, USA), and the tissue is fixed in formalin and embedded in paraffin. Two independent third-party pathologists who are unaware of the patients’ treatment assignment, biopsy sequence and clinical outcome will examine all biopsy slides.

Hepatic fibrosis is assessed by the METAVIR system for fibrosis stage and necroinflammatory activity as a hard index [22, 23]. The fibrosis stages are: no fibrosis (F0), mild fibrosis (F1), moderate fibrosis (F2), severe fibrosis (F3) and cirrhosis (F4). Necroinflammatory activity is: no activity (A0) mild activity (A1), moderate activity (A2) and severe activity (A3). Serum fibrosis biomarkers including Fibrotest, aspartate aminotransferase to the platelet ratio index (APRI), liver stiffness spleen diameter to platelet ratio score (LSPS), and FibroMeters and FibroScan are used to assess hepatic fibrosis as a surrogate index [24, 25]. Hard and surrogates indexes are evaluated at all three time points (baseline, week 72 and week 96 after the open label) for each patient. Changes in liver fibrosis from baseline to weeks 72 and weeks 96 after the open label are analyzed on available pooled data using the METAVIR scoring system and the surrogate index.

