### Follow-up

At baseline, all patients are screened to confirm the absence of HCC using abdominal ultrasonography and laboratory analyses, including AFP level. During the follow-up, all patients are seen at 3- to 6-month intervals. Periodic surveillance is also performed with abdominal ultrasonography and laboratory analyses, including AFP level, every 3 or 6 months to screen for HCC and other complications related to portal hypertension. Patients also undergo endoscopy every 1 or 2 years for screening and follow-up of gastroesophageal varices. HBV DNA, hepatitis B surface antigen (HBsAg), anti-HBs, hepatitis B e antigen, anti-HBe, and routine hematological and biochemical tests are performed. Adverse events that have occurred since the previous visit are recorded, and toxicity is graded according to predefined criteria.

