### Participants and eligibility

Inclusion criteria are as follows: (1) men or women aged 18 to 65 years; (2) persistent serum HBsAg for ≥6 months; (3) serum HBV DNA ≥2000 IU/mL or ≥10,000 copies/mL; (4) baseline liver fibrosis (liver biopsy) stage F ≥2 (METAVIR system); (5) TCM syndrome type: blood stasis, or blood deficiency with toxic heat retention and (6) no antiviral or antifibrotic therapy for 6 months. Patients are excluded if they have any of the following at enrollment: (1) history of concurrent malignancy, including HCC; (2) baseline liver fibrosis (liver biopsy) stage F <2 (METAVIR system); (3) immunosuppression (organ transplantation or immunosuppressant use); (4) severe alcoholism; (5) serious uncontrollable heart, kidney, lung, endocrine, blood, metabolic or gastrointestinal primary disease, or mental illness; (6) pregnancy or lactation; (7) allergic constitution or allergic to TCM use; (8) no prescribed medication, poor compliance, incomplete data affecting the efficacy and safety of those judgments; (9) unsuitable for this trial according to the researchers or (10) co-infection with hepatitis C or D virus or HIV.

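### The safety set and full analysis set share a rule that requires a post-dose efficacy evaluation, and the per-protocol rule excludes anyone who dies before the last scheduled visit

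*Protocol article*

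**What the plan says.** Statistical methods in the protocol article defines the sets in two sentences. The first covers two sets at once: "The randomized subjects who have taken at least one dose of study drug" and who "are evaluated for at least once curative effect after taking medication, constitute the full analysis set and safety analysis set". Both conditions must be met, for safety as well as for efficacy. The article does not define an evaluation of curative effect. The second sentence is the whole per-protocol rule: "Those who complete all the visits comprise the per-protocol set". It makes no exception for death and states no adherence or deviation criterion.

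Other parts of the article bear on these rules:

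- Study design: "The primary end points in this study are the occurrence of HCC or liver-related mortality", and "Secondary end points are disease progression and overall survival rate".
- Statistical methods: "Cumulative incidence of HCC and overall survival rate will be determined by Kaplan–Meier analysis, and the log-rank test will be used for treatment comparisons". No analysis set is named for this.
- Follow-up: "During the follow-up, all patients are seen at 3- to 6-month intervals".
- Safety: every adverse event is to be recorded, whatever its cause.
- Statistical methods also promises, for each group, the rate of loss caused by adverse events.

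**The concern.** A safety population should depend on exposure alone. Here it also depends on an efficacy assessment that comes after dosing. The patients left out are those who start the drug and stop early, which is where early intolerance would show.

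The same condition applies to the full analysis set. HCC and death are events counted from randomization, and a patient needs no efficacy evaluation to contribute follow-up time or an event. Selecting patients on something that happens after randomization gives up part of the protection that randomization provides.

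The per-protocol rule selects on survival. Death is part of the primary end point and defines a secondary one, yet a patient who dies before the last scheduled visit fails the rule because of the outcome itself.

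These are rules that the article states, not details left out of it. An analysis plan that follows this wording would carry them forward.

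**Working it through.** The plan gives no figure for this point, so there is none to reproduce. The check applies the stated rules to two kinds of patient and then sizes the result under stated assumptions.

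**1. A dosed patient who leaves early**

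- Randomized: yes. At least one dose: yes. Post-dose evaluation of curative effect: no.
- Result: outside the full analysis set and outside the safety set.
- Set beside the Safety section, this patient's adverse event is recorded but has no place in the safety set. Set beside the promised loss rate due to adverse events, the patient is a loss that the defined denominator cannot hold.
- Length of the window: follow-up visits are 3 to 6 months apart. If a scheduled follow-up visit is what counts as an evaluation, and none falls earlier, the window is about 3 to 6 months.

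**2. Size of the early loss (assumed)**

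The article gives no early withdrawal rate. With 500 per arm (Randomization) and an assumed fraction *e* who are dosed and leave before an evaluation, the number lost is 500 × *e*:

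| Assumed *e* | Lost per arm | Left in the safety set, if all 500 were dosed |
|---|---|---|
| 1% | 5 | 495 |
| 3% | 15 | 485 |
| 5% | 25 | 475 |

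If 20% to 50% of them left because of an adverse event (also assumed), the uncounted cases run from 5 × 0.20 = 1 to 25 × 0.50 = 12.5 per arm.

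**3. A patient who dies before the last scheduled visit**

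- All visits completed: impossible. Result: outside the per-protocol set.
- In that set the number of deaths at every time up to the last visit is therefore d = 0. The Kaplan–Meier estimate is the product of (1 − d/n) over event times, which equals 1, so survival is 100% in both arms.
- With no event times, the log-rank observed-minus-expected difference is 0 and its variance is 0. The test cannot be computed.

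The article gives no death rate. At an assumed 1%, 3% or 5% mortality before the last visit, 500 × rate = 5, 15 or 25 deaths per arm would be removed, and survival would read 100% instead of 99%, 97% or 95%.

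**The case against.** The strongest reply has four parts.

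- *The per-protocol set is never assigned to survival.* This is true. The Kaplan–Meier and log-rank sentence names no set, and the assignment may sit in an analysis plan that is not shown. A reader might infer that the planned mortality analysis is meaningless, or that every death is lost. The article supports neither. Deaths after the last scheduled visit are not excluded, and the full analysis set keeps deaths that follow an efficacy evaluation.
- *Early adverse events are still recorded, and losses due to them are to be reported.* This is also true, and it means the data should exist. It does not repair the set definition, and it is what makes the definition inconsistent with the rest of the article.
- *The full analysis set rule is mild.* One dose and one evaluation is not a compliance threshold, and the trial is double-blind with placebo. A claim that the arms are no longer comparable would go too far: nothing shows that early loss differs by arm, and the direction of any bias is unknown.
- *The loss could be trivial.* This cannot be settled from the article. One might spread the 15% drop-out allowance in Sample size evenly over 24 months: 0.15 × 3/24 × 1,000 = 18.75 and 0.15 × 6/24 × 1,000 = 37.5, or about 19 to 38 patients. That allowance belongs to the fibrosis-reversal calculation and is not a forecast of early loss. The figure also assumes even drop-out, that every leaver was dosed, and that none was evaluated earlier. It should not be used as an estimate.

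Three further readings are tempting and not supported:

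- The exclusion criterion "no prescribed medication, poor compliance, incomplete data affecting the efficacy and safety of those judgments" might seem to permit removal of patients after randomization. The sentence that opens the list confines it to the time of enrollment, and the set definitions do not refer to it.
- Patients with HCC might seem to leave the per-protocol set when they are offered open-label treatment. Nothing says that their visits stop or no longer count.
- If curative effect meant histology only, the first on-treatment biopsy is at week 72 and at most 45% are expected to have a second one, so at least 55% would fall outside both sets. The article does not force this reading: Statistical methods also compares liver function, ultrasound and TCM syndrome.

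**Conclusion.** The point holds in two parts.

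First, the shared definition leaves any dosed patient without a post-dose efficacy evaluation out of both the safety set and the full analysis set. This follows from the wording alone. The number is unknown: 5 to 25 per arm if 1% to 5% are lost in this way, which is an assumption. Later drop-outs are not affected. A patient who dies early is also lost, unless the death itself is taken as an evaluation, which the article does not say.

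Second, the per-protocol set contains no deaths before the last scheduled visit, by construction. That would empty a per-protocol analysis of overall survival up to that visit, and of the liver-related death component of the primary end point. Whether it matters in practice depends on how the set is used, which the article does not state.

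**What to change.** Replace the two defining sentences in Statistical methods with separate definitions:

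- **Safety set:** all patients who took at least one dose, grouped by treatment received.
- **Efficacy set for HCC, liver-related death and overall survival:** all randomized patients, as randomized, followed from randomization and censored at last contact.
- **Per-protocol set:** patients without a major protocol deviation. Death and HCC count as outcomes and never as missed visits.

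State which set serves each end point. No change to the exclusion criteria is needed for this point. The cost is protocol and analysis-plan wording only: the sample size and the visit schedule stay as they are. The change is best made before any unblinded data are seen.

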**Methods/design:**

This multicenter, centrally randomized, double-blind, placebo-controlled, parallel-group study is planned to complete within 5 years. For the study, 1,000 with CHB or HBV-related compensated cirrhosis are randomly assigned in a 1:1 ratio to a treatment group (0.5 mg ETV once daily; 2 g RGT three times daily) or a control group (0.5 mg ETV once daily; 2 g RGT dummy agent three times daily). The primary end points are the development of HCC and liver-related death. Secondary end points include disease progression and overall survival.

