### Sample size

We assumed that the rate of hepatic fibrosis reversal would be 39% in the ETV-treated patients at the end of 2 years [26, 27], and 61% in the RGT-treated patients. Using PASS 2002 statistical software (NCSS, Kaysville, UT, USA), we calculated that we need two groups of 186 cases, and each group needs to enroll 223 cases if there is a drop-out rate of 15%, that is, a total of 446 cases. Currently, up to 45% of all enrolled patients will be accepted for a second liver biopsy. A total of 500 cases is required in each group to achieve a power of 0.80 and a significance level of 0.05 in assessing the difference between the two groups.

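### The declared primary end point is HCC and/or liver-related mortality, but the analyses named are for HCC alone and for overall survival, so none of them tests it

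*Protocol article*

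**What the plan says.** Four statements in the protocol article bear on this point.

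- **Abstract, Methods/design:** "The primary end points are the development of HCC and liver-related death".
- **Study design, text after Figure 1:** "The primary end points in this study are the occurrence of HCC or liver-related mortality". The same paragraph adds: "Liver-related mortality is defined as death caused by hepatic decompensation (regardless of etiology) or HCC".
- **Study design, following paragraph:** "Secondary end points are disease progression and overall survival rate".
- **Statistical methods:** "Cumulative incidence of HCC and overall survival rate will be determined by" Kaplan–Meier analysis, with the log-rank test for comparing the arms. One threshold is set for everything: "The statistical significance is defined as a two-sided" P below 0.05.

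Statistical methods goes on to name tests for METAVIR change, liver and spleen ultrasound, serum fibrosis markers, FibroScan and TCM syndrome. It names none for liver-related mortality, either alone or combined with HCC.

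**The concern.** The analysis that is written down does not match the end point that is written down. Of the two time-to-event outcomes given a test, one is only part of the primary end point and the other is secondary.

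The omitted part may matter. Patients with compensated cirrhosis are among those studied, and the second aim in the Background is to prevent or delay decompensation. Deaths from decompensation without HCC are therefore outcomes that the trial itself regards as relevant. If they do not count in the main comparison, an arm with more of them is not penalised for them there.

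The *and*/*or* ambiguity adds to this. Someone reading the results could not tell from this text whether the trial's primary claim rests on HCC, on a composite, or on both outcomes separately. The choice could be made after the data are seen. The Data and Safety Monitoring Board section also allows termination once superiority is shown, and it is not clear on which outcome.

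**Working it through.** **Step 1. Set the end point against the analysis, on each reading.**

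| Reading of the primary end point | Analysis it needs | Named in Statistical methods? |
|---|---|---|
| Composite: first of HCC or liver-related death | Time-to-event test of the composite | No |
| Two end points: HCC | Time-to-event test of HCC | Yes |
| Two end points: liver-related death | Time-to-event test of liver-related death | No |

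The mismatch holds on both readings.

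**Step 2. See where each liver death goes under the named analyses.**

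- Death from HCC after HCC was diagnosed: already an event in the HCC analysis.
- Death from decompensation with no prior HCC: not an HCC event. The article states no censoring rule, but a Kaplan–Meier analysis of HCC can do nothing with this patient except censor at death. The death counts in overall survival, mixed with deaths from all other causes.

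**Step 3. Size.** The plan has no figure to reproduce here. The sample size rests on fibrosis reversal ("We assumed that the rate of hepatic fibrosis reversal would be 39% in the ETV-treated patients at the end of 2 years", against 61% with RGT). No event rate, hazard ratio or event count is given for HCC or liver-related death. What follows uses assumed values.

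Let *h* be the yearly hazard of HCC and *l* the yearly hazard of liver death without HCC, both constant. The share of first primary events that are liver deaths without HCC is *l* / (*h* + *l*). Under constant hazards this share does not depend on length of follow-up.

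| *h* (assumed) | *l* (assumed) | *l* / (*h* + *l*) | Share not counted in the HCC test |
|---|---|---|---|
| 2% | 0.5% | 0.5 / 2.5 | 20% |
| 3% | 1% | 1 / 4 | 25% |
| 2% | 1% | 1 / 3 | 33% |
| 3% | 2% | 2 / 5 | 40% |

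These four pairings give 20–40%. Taking every combination of the two ranges would widen this to 0.5 / 3.5 = 14% at one corner and 2 / 4 = 50% at the other.

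**The case against.** The best defence is that this is a condensed article. Its Statistical methods section does not claim to be exhaustive: it also names no test for decompensated cirrhosis, which is part of a secondary end point. Censoring rules, competing-risk methods and multiplicity commonly sit in a statistical analysis plan, which is not shown. That stands for those details, and the point does not rest on them. It does not cover the mismatch itself, because the section is not silent: it names its time-to-event outcomes and pairs part of the primary end point with a secondary one.

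A second defence is that both statements of the primary end point use the plural, so *or* need not mean a composite. That is fair. The charge is ambiguity, not outright contradiction.

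A third is that the first aim in the Background concerns HCC itself, so an HCC-only analysis answers the lead question. That would be coherent, but only if the declared primary end point were changed to match.

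A reader might also infer more than the text supports:

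- **That liver-related death is never analysed.** Such deaths do enter overall survival. They are never analysed as part of the primary end point.
- **That all liver deaths are censored from the HCC curve.** Only those without prior HCC are, and this follows from the method rather than from a stated rule.
- **That the HCC comparison is itself invalid or badly biased.** A log-rank test with competing deaths censored is a valid comparison of cause-specific HCC hazards. At five years the curve's overstatement is small: with hazards of 2% and 1%, 1 − exp(−0.10) = 9.5% against (2/3)(1 − exp(−0.15)) = 9.3%; with 3% and 2%, 1 − exp(−0.15) = 13.9% against (3/5)(1 − exp(−0.25)) = 13.3%.
- **That the type I error is inflated.** The article names no test of liver-related death and no success rule for two tests, so there is no stated procedure whose error could be computed.
- **That a definite amount of power is lost.** No event counts or effect sizes are given for these outcomes.

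**Conclusion.** The point holds and the text is wrong as written: no analysis named in Statistical methods tests the declared primary end point, whether that is a composite or two end points. This rests on the wording alone and needs no assumption.

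The size cannot be taken from the article. The 20–40% of first primary events not counted is an illustration that depends entirely on assumed constant hazards and on the four pairings chosen. It shows that the omitted part need not be negligible; it does not estimate what this trial will see. It also says nothing about the direction of any effect on the treatment comparison.

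**What to change.** In Statistical methods, state the structure of the primary end point and name the test that matches it.

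- **Preferred:** time from randomisation to the first of HCC or liver-related death, compared by one log-rank test at two-sided 0.05, with HCC and liver-related death each reported as components. Time to first event also suits the design, since Study design offers open-label treatment to patients who reach an end point. A separate test of death after HCC would mix randomised and open-label exposure.
- **If two separate end points are intended:** name a test for liver-related death and state the rule for success, that is, whether either or both must be significant and how the error rate is held.

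Then bring the Abstract and Study design into line, so that all three places describe the same end point.

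The cost is wording and minor programming; no new data are needed, because HCC and cause of death are already required by the end point definitions. The one small downside of the composite is that it could dilute an effect specific to HCC. The component report would show this.
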